### 9.8.2 *Procedures for discontinuation of a subject from the study*

A subject who prematurely discontinues participation in the study will always be asked about the reason(s) for discontinuation and the presence of any AEs. If a subject withdraws consent,

the investigator must ask the subject if he/she is willing, as soon as possible, to be assessed according to the procedures scheduled for Visit 6 and Visit 13 visit in each part. Any ongoing AEs will be followed as described in Section 11.7.1.14.

The primary reason for discontinuation/early withdrawal must be specified in the end-of-treatment form of the eCRF and final drug accountability must be performed.

#### 9.8.2.1 Subject replacement

Subjects who are randomized but not dosed may be replaced as may subjects who were prematurely withdrawn from the study for any reason except the occurrence of AEs assessed at least possibly related to the IMP. Subjects withdrawn after Visit 6 (SAD part) or Visit 13 (MAD part) will not be replaced.

### 9.9 Randomization

The randomization in the SAD part of study will be done by arm, i.e. either active treatment to the right arm and placebo to the left arm or vice versa. Each arm will have 2 wounds which will be on same location on both arms.

The randomization in the MAD part of the study will also be done by arm, i.e. active treatment to 4 wounds to the right arm and placebo and saline to 2 wounds each on the left arm or vice versa. The wounds will be placed on the same location on both arms. For details, refer to Table 9.9-1.

A computer-generated randomization list will be created using SAS Proc Plan, SAS Version 9.4. The randomization list will be kept by the randomizer in a sealed envelope until database lock (DBL). A copy of the randomization list will be kept by an unblinded pharmacist at the site.

Sealed individual, treatment code envelopes will be kept in a locked and restricted area at the research clinic in case of need for emergency unblinding and at [REDACTED]

**Table 9.9-1 Example of randomization (MAD)**

| Sequence | Location (seen from shoulder) | Treatment |
|----------|-------------------------------|-----------|
| 2101     | L1 and L2                     | NaCl      |
|          | L3 and L4                     | Placebo   |
|          | R1, R2, R3 and R4             | Active    |
| 2102     | L1 and L2                     | Placebo   |
|          | L3 and L4                     | NaCl      |
|          | R1, R2, R3 and R4             | Active    |
| 2103     | L1, L2, L3 and L4             | Active    |
|          | R1 and R2                     | NaCl      |
|          | R3 and R4                     | Placebo   |
| 2104     | L1, L2, L3 and L4             | Active    |
|          | R1 and R2                     | Placebo   |
|          | R3 and R4                     | NaCl      |
| Etc.     |                               |           |

## 9.10 Blinding

This is a double-blind study and the allocation of treatments will not be disclosed to clinical staff involved in study-related evaluations nor to independent evaluators until the 12 months long-term follow-up visit in each part has been conducted.

The activated ILP100-DP is a pale-yellow to yellow solution. Placebo and saline are transparent solutions. Every effort will be made at the research clinic in order to maintain the blind. Both the activated ILP100-DP, the placebo and the saline solutions will be masked in such a way that study subjects and study staff will remain blinded during the study. An unblinded pharmacist will prepare the activated ILP100-DP/placebo/saline under supervision of an unblinded study nurse or delegate. The procedure will be documented by video recording. Unblinded staff will also apply the IMP, see Section 10.6. The unblinded staff will not be involved in any study-specific evaluations (study-specific evaluations do not include sample handling). Once the adhesive film has been applied on each wound it is not possible to distinguish between the treatments.

The subjects will be blindfolded during the administration procedure.

## 9.11 Emergency unblinding during the study

The treatment code may only be broken by the study medical staff in case of emergency when knowledge of the treatment received is necessary for the proper medical management of the subject. The code breaking procedure should be carefully documented.

The randomization code may be broken by the iSRC during the assessment process (partial unblinding) to enable their decision on continued dosing of further cohorts or to stop the dose escalation, see Section 8.4.1. The medical staff and the subjects will still be blinded for the treatments to be administered in the subsequent cohorts in order to minimize bias (see Section 8.4.3).

For unblinding procedures in case of a potential suspected unexpected serious adverse reaction (SUSAR), refer to Section 11.7.1.13.

# 10 TREATMENTS

## 10.1 Identity of investigational medicinal products

The API is living, genetically modified *L. reuteri* R2LC bacteria transformed with a plasmid, pSIP411 with the sequence for the human chemokine CXCL12-1a inserted behind an inducible promoter, referred to as the drug substance. The drug product, ILP100-DP, is the lyophilized drug substance for topical use.

ILP100-DP is a GTMP type of ATMP classified as per Article 2 (1)(a,b) of Regulation (EC) No 1394/2007. The activated ILP100 DP is classified as a low risk microbe that and will hence be handled at BSL-1.

The **drug product ILP100-DP** will be provided in a freeze-dried formulation in a glass vial. Besides the drug product, the formulation contains ascorbic acid and sucrose. One strength of ILP100-DP will be provided:  $5 \times 10^9$  CFU/vial.

The **activator is the peptide SppIP** that induced the expression of CXCL12 by binding to the promoter in the expression vector. The activator is formulated in sterile 2.5 mM acetate buffer, pH 4.0 in a glass vial referred to as the SppIP solution.

**Buffer A** is used to dissolve ILP100-DP. Buffer A is a 45 mM acetate buffer, pH 5.5.

**Buffer B** is used to dilute ILP100-DP to 2 additional strengths. Buffer B is a 0.5% ascorbic acid w/v, 19% sucrose w/v, 60 mM phosphate, 45 mM acetate buffer, pH 4.7.

**Buffer C** is used to dilute the activator before use. Buffer C is a 2.5 mM acetate buffer, pH 4.0.

Buffer A, B and C are sterile and provided in separate glass vials.

The different doses of ILP100-DP will be prepared by dilutions in Buffer B. Before use, the diluted ILP100-DP will be mixed with the activation peptide SppIP to generate the ready-to-use product referred to as **activated ILP100-DP**. The activation should be done between 30 minutes and 8 hours after dilution of ILP100-DP. The activated ILP100-DP must be administered to subjects from 20 minutes to 2 hours after activation.

**Placebo** is Buffer B (0.5% ascorbic acid w/v, 19% sucrose w/v, 60 mM phosphate, 45 mM acetate buffer, pH 4.7) mixed with the activation peptide SppIP (SppIP solution).

The concentration of the activation peptide SppIP in the reconstituted products (activated ILP100-DP and placebo) is 100 ng/mL.

A separate IMP preparation manual detailing all steps needed to prepare activated ILP100-DP at different doses and placebo will be provided.

**Sterile Saline (0.9 % NaCl)** will be used as a “**no treatment**” control in the MAD part of the study. This solution will be administered in the same volume as the active treatment and placebo.

The start and stop time for the IMP application will be recorded in the eCRF (first wound and last wound).

## 10.2 Identity of non-investigational medicinal products

Not applicable.

## 10.3 Manufacturing, packaging and labelling

ILP100-DP, dilution buffers A, B and C, SppIP solution and placebo will be manufactured, packaged and released by [REDACTED]

The labelling of the IMP (including saline) will be performed by [REDACTED].

Labels will comply with applicable Good Manufacturing Practice (GMP) requirements in accordance with EudraLex Volume 4, Annex 13, 2010 and will contain information describing that the drug product is a GMO.

The labelled IMP will be shipped to the research clinic [REDACTED]

#### 10.4 Conditions for storage

ILP100-DP (lyophilized powder), the SppIP solution and saline will be stored in an access-controlled refrigerator at +2°C to +8°C at [REDACTED]. Other solutions will be stored in an access-controlled freezer below -20°C at [REDACTED].

Diluted ILP100-DP must be stored at room temperature for at least 30 minutes prior to activation but may be stored at room temperature for up to 8 hours prior to activation.

Ready-to-use activated ILP100-DP and placebo must be stored at room temperature for at least 20 minutes after activation but may be stored at room temperature for up to 2 hours prior to application.

Temperature logs will be kept for the areas where the IMP is stored. The temperature should be noted on a daily basis (working days only unless automatic temperature readings are available).

#### 10.5 Dispensing and accountability

The ready-to-use activated ILP100-DP and placebo will be prepared by a trained, unblinded pharmacist as briefly described in Section 10.1 and as detailed in a separate IMP preparation manual. A second unblinded person will oversee the preparation and dispensing process, which will be documented by video recording.

Dispensed IMP will be labelled with the following information:

- Study code
- Subject ID
- Dosing Day
- Blinded treatment ID
- Contains GMO

[REDACTED] and the Investigator will maintain a Storage and Accountability log and a Drug Dispensing Log detailing the dates and quantities of study medication received, dispensed to and used by each subject and study medication returned or destroyed at the end of the study. Any discrepancies between dispensed and returned IMP must be explained and documented. Products deliberately and/or accidentally destroyed by the site or the subject must be accounted for.

#### 10.6 Treatment administration and dressing

The IMP will be administered topically on each wound by site staff in the morning of each treatment day.

Before use, diluted ILP100-DP or placebo will be mixed with the activator to generate the ready-to-use activated ILP100-DP and the placebo product, respectively, see Section 10.1 and Section 10.5. The concentration of the activation peptide SppIP in the reconstituted products will be 100 ng/ml. Detailed IMP preparation instructions will be provided separately.

The proposed dose levels in the SAD part are:  $5 \times 10^4$ ,  $5 \times 10^7$  and  $1 \times 10^9$  CFU/cm^2 wound area.

The proposed dose levels in the MAD part are:  $5 \times 10^5$ ,  $5 \times 10^7$  and  $1 \times 10^9$  CFU/cm^2 wound area.

Analysis of the dose formulation (viable count) will be performed on Day 1 (SAD and MAD, first cohort) and Day 19 (MAD, all cohorts) by [REDACTED]

Using a pipette, 50 µL IMP solution will be applied in the center of each wound. Two unblinded persons will take part of the administration process, one will perform the application of IMP and the other one will confirm that the correct treatment is administered to the intended wound, i.e. in accordance with the randomization list. The IMP administration will be documented by video recording. After application, each wound will be dressed with an adhesive, transparent film that will protect the wounds and isolate them from each other. Separate, non-overlapping dressings will be used for each wound. Any leakage of the treatment(s) outside the film should be commented on in the eCRF. An elastic, tubular bandage will be used on top of the films.

Following IMP administration, the wounds will be covered with adhesive, transparent film around the clock for 2 days and 2 nights (except during wound evaluations and IMP application). From Day 3 and onwards, the wounds will be treated with IMP and covered with adhesive, transparent film for 1 hour after IMP application where after the film will be removed. The wounds will be allowed to air dry and will then be separately covered with a non-occlusive dressing that can be used during showering and protects against contamination of viruses and bacteria.

At visits outlined in Table 8.1-2, the dressings will be removed and stored in -70 for future analysis (Section 11.9.3) and the area around the wound will be cleaned if necessary. Following wound photography (Section 11.5), assessment of local tolerability reactions (Section 11.7.6) and IMP application (multiple dosing in MAD only), new dressing material will be used to cover each wound. An elastic, tubular bandage will be used on top of the films.

## **10.7 Continuation of treatment with Investigational Medicinal Product**

This is a Phase I study in healthy volunteers who will have no medical benefit from the treatment. There will be no treatment with activated ILP100 DP after end of study participation.

## **10.8 Treatment compliance**

All IMP will be administered at the research clinic by clinical staff to ensure compliance. Any leakage of the treatment(s) outside the film should be commented on in the eCRF.

## **10.9 Return and destruction of investigational medicinal products**

Any unused study medication will be returned to the Sponsor for destruction. Empty containers will be destroyed at the study site. The Monitor will perform final IMP accountability reconciliation at the study end to verify that all unused IMP is adequately destroyed/returned and documented.

## 11 STUDY ASSESSMENTS

The study assessments are described in the sections below and the timing of these assessments are detailed in the schedule of events; Table 8.1-1 and Table 8.1-2.

### 11.1 Recording of data

The Principal Investigator will provide the Sponsor with all data produced during the study from the scheduled study assessments. He/she ensures the accuracy, completeness, legibility, and timeliness of the data reported to Sponsor in the eCRF and in all required reports.

### 11.2 Procedures to mitigate and monitor environmental spread of gene modified organisms

In order to address the general environmental risk assessments on the release of GMOs into the environment highlighted in 2002:1086, [REDACTED] will follow general procedures for handling of high risk clinical waste in the clinic (e.g. HIV contaminated material) and also perform specific investigations on potential environmental spread of *L. reuteri* R2LC with pSIP411 in wound dressings from subjects, presence on the skin surface outside the wound area, presence in feces, presence in waste water from water locks at the research clinic.

For details regarding potential risks, their likelihood and risk management to reduce the likelihood of risks, refer to the ERA.

### 11.3 Demographics and other baseline characteristics

#### 11.3.1 *Informed consent*

Signed informed consent must be obtained before any screening procedures are initiated.

The informed consent procedure is further described in Section 14.3.

#### 11.3.2 *Eligibility criteria*

Eligibility criteria should be checked during screening and verified before randomization. The criteria are specified in Sections 9.4 and 9.5.

#### 11.3.3 *Demographic information*

The following demographic data will be recorded: gender, age, ethnicity, race and dominant hand.

#### 11.3.4 *Weight and height*

Weight and height will be measured without shoes. BMI will be calculated from the height and weight recorded.

#### 11.3.5 *Medical/surgical history*

Medical/surgical history will be obtained by subject interview in order to verify that the eligibility criteria are met.

#### 11.3.6 *Prior and concomitant medication*

Prior medication will be obtained by subject interview in order to verify that the eligibility criteria are met (see also Section 9.6.2).

Medications are classified as prior if the stop date was before or on the day of the first dose administration (pre-dose) and as concomitant if ongoing on the day of the first dose administration, stopped after the first dose administration or started after the first dose administration.

Any use of concomitant medication from screening until the last end-of-study visit must be documented in the subject's eCRF. Relevant information (*i.e.* name of medication, dose, unit, frequency, start and stop dates, reason for use) must be recorded. All changes in medication should be noted in the eCRF.

On Day 1 in each part, the time of administration of any concomitant medication, or stop of any concomitant medication, must be given in the eCRF.

#### 11.3.7 *HIV and Hepatitis B/C*

Subjects will be tested for HIV and hepatitis B/C prior to inclusion into the study in order to protect personnel handling the blood and tissue samples.

#### 11.3.8 *Pregnancy test*

All females will do a pregnancy test at screening (blood/serum) and at additional visits (urine) specified in Table 8.1-1 and Table 8.1-2.

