### **Long-term follow-up (Visit 7 to Visit 14)**

After Visit 6, a 5-year long-term follow-up period (Visits 7 to 14) will be initiated. During the first year, subjects will visit the research clinic 6 weeks and 3, 6 and 12 months after treatment (Visit 7 to Visit 10). Following Visit 10, subjects will be followed-up once yearly by visits to the research clinic (Visit 11 to Visit 14).

Physical examination, AE and concomitant medication questioning, blood sampling for CXCL12 ADA analysis, photography (standard camera and 3D camera), local tolerability assessment (investigator), assessment of scar tissue formation, skin swab and feces sampling for analysis of presence of *L. reuteri* will be performed at visits outlined in Table 8.1-1.

Subjects will be urged to contact the clinic in between visits, including long-term follow-up visits, in case of e.g. development of any new/recurrent cancer, development of infection, immunogenicity related reactions or local reactions associated with the wound/scar area. If considered relevant by the Investigator, extra visits will be scheduled.

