be checked as detailed in Table 8.1-2. There is immediate access to equipment, qualified staff and an ICU in case of an acute emergency. Up to 4 subjects will be dosed on the same day.

The wounds will be photographed in a standardized setting according to instructions specified in a separate manual, and briefly summarized in Section 11.5, before treatment on Day 1, pre-treatment at the subsequent dosing visits, and at all follow-up visits to the research clinic. Selected members of the clinical staff will receive photography training prior to handling of the camera equipment. In addition, wounds will be analyzed using a 3D camera as outlined in Section 11.9.1.

Following the first dose on Day 1, subjects will come for 10 additional visits between Day 2 and Day 21 (Visits 3 to 12). The last dose will be given on Day 19 (Visit 11). Safety will be assessed by vital signs, safety laboratory parameters, local tolerability, AEs, use of concomitant medications and CXCL12 ADA analysis at visits outlined in Table 8.1-2.

The wounds must not at any visit be cleaned (unless necessary for safety reasons, e.g. due to an infection). The area surrounding the wounds should then be carefully cleaned with water if necessary. At visits when swabbing is performed, the area around the wound should be cleaned after swabbing if necessary. Before the subject leaves the research clinic, the wound should be dressed until healed.

Blood sampling for analysis of CXCL12 and *L. reuteri* systemic levels and a swab of the area surrounding the wounds and feces sampling for analysis of any presence of *L. reuteri* R2LC colonies containing the pSIP411 plasmid will be performed at time points and visits specified in Table 8.1-2.

For exploratory purposes, microcirculation assessments will be performed and dressings will be collected at time points outlined in Table 8.1-2.

An end-of-treatment phase visit (Visit 13) will take place on Day 32 ( $\pm 1$  day) or after early withdrawal.

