### **Long-term follow-up (Visit 14 to Visit 21)**

After Visit 13, a 5-year long-term follow-up period (Visit 14 to 21) will be initiated. During the first year, subjects will visit the research clinic 6 weeks and 3, 6 and 12 months after treatment (Visit 14 to Visit 17). Following Visit 17, subjects will be followed-up yearly by visits to the research clinic.

Physical examination, AE and concomitant medication questioning, blood sampling for CXCL12 ADA analysis, photography (standard camera and 3D camera), local tolerability assessment (investigator), assessment of scar tissue formation, skin swab and feces sampling for analysis presence of *L. reuteri* will be performed at visits outlined in Table 8.1-2.

Subjects will be urged to contact the clinic in between visits, including long-term follow-up visits, in case of e.g. development of any new/recurrent cancer, development of infection, immunogenicity related reactions or local reactions associated with the wound/scar area. If considered relevant by the Investigator, extra visits will be scheduled.

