|                                                |                 |                           | Time points in relation to first dose (Day 1)                 |       |                                                         |                   |                                     | Time points in relation to last dose (Day 19) |                      |                      |                       |                          |                      |
| Assessment / Day                               | Day -28 to -1   | Day 1                     | Day 2                                                         | Day 3 | Day 5, 8, 10, 12, 15, 17, 19
±1 day on Days 12 to 19 | Day 21
± 1 day | Day 32
± 1 day                   | 6 weeks
± 3 days                           | 3 months
± 1 week | 6 months
± 1 week | 12 months
± 1 week | Once yearly
± 2 weeks | 5 years
± 1 month |
| Informed Consent                               | X               |                           |                                                               |       |                                                         |                   |                                     |                                               |                      |                      |                       |                          |                      |
| Inclusion/exclusion criteria                   | X               | X           |                                                               |       |                                                         |                   |                                     |                                               |                      |                      |                       |                          |                      |
| Demographics                                   | X               |                           |                                                               |       |                                                         |                   |                                     |                                               |                      |                      |                       |                          |                      |

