| Urine drug screen                  | X               | X             |                                                               |       |                                                         | X                 | X                                   | X                                             | X                    | X                    | X                     | X                        | X                    |
| Alcohol breath test                            | X               | X             |                                                               |       |                                                         | X                 | X                                   | X                                             | X                    | X                    | X                     | X                        | X                    |
| Pregnancy test                                 | X   | X             |                                                               |       |                                                         | X     | X                                   |                                               |                      |                      |                       |                          |                      |
| 12-lead safety ECG                             | X               | X           |                                                               |       | X                                           |                   | X                                   |                                               |                      |                      |                       |                          |                      |
| Vital signs (BP & pulse)                       | X               | X           |                                                               | X     | X                                                       | X                 | X                                   |                                               |                      |                      |                       |                          |                      |

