## 9.4 Inclusion criteria

For inclusion in the study, subjects must fulfil the following criteria:

1. Willing and able to provide a written informed consent for participation in the study.
2. Healthy males and females aged  $\geq 25$  and  $\leq 45$  years.
3. Willing and able to comply with study requirements.
4. Non-obese subjects with a body Mass Index (BMI)  $\geq 18.0$  and  $\leq 30.0$  kg/m^2 and weight at least 50 kg and no more than 120 kg at screening.
5. Clinically normal medical history, physical findings, vital signs, ECG and laboratory values at the time of screening, as judged by the Investigator.
6. Women of child bearing potential (WOCBP) must agree to use a highly effective method of contraception with a failure rate of  $< 1\%$  to prevent pregnancy (combined [estrogen and progestogen containing] hormonal contraception associated with inhibition of ovulation [oral, intravaginal, transdermal], progestogen-only hormonal contraception associated with inhibition of ovulation [oral, injectable, implantable], intrauterine device [IUD] or intrauterine hormone-releasing system [IUS]) from at least 4 weeks prior to dose until 3 months after the last dose of IMP and until confirmation of negative 6 weeks skin swab and feces analyses concerning *L. reuteri* R2LC and/or pILP100 findings. Their male partner must agree to use a condom during the same time frame.

Women of non-childbearing potential are defined as pre-menopausal females who are sterilized (tubal ligation or permanent bilateral occlusion of fallopian tubes); or post-menopausal defined as 12 months of amenorrhea (in questionable cases a blood sample with simultaneous detection of follicle stimulating hormone [FSH] 25-140 IE/L and estradiol  $< 183$  pmol/l is confirmatory).

Male subjects must be willing to use condom or be vasectomized to prevent pregnancy and drug exposure of a partner and refrain from donating sperm from the date of dosing until 3 months after the last dose of IMP and until confirmation of negative 6 weeks skin swab and feces analyses concerning *L. reuteri* R2LC and/or pILP100 findings. Their female partner of child-bearing potential must use contraceptive methods with a failure rate of  $< 1\%$  to prevent pregnancy (see above).

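### Scheduled pregnancy testing ends 13 days after the last of ten doses in the MAD but 42 days after the single dose in the SAD, under one contraception rule and with no reason given

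*Protocol*

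**What the plan says.** Protocol Section 11.3.8 sets the type of test and refers to the tables for the visits: "All females will do a pregnancy test at screening (blood/serum) and at additional visits (urine) specified in Table 8.1-1 and Table 8.1-2". Neither that section nor the footnote to the test row in either table explains the choice of visits.

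- **SAD (Table 8.1-1).** The row is marked at Visit 1 (screening), Visit 2 (Day 1), Visit 6 (Day 14) and Visit 7 (6 weeks). Section 8.1.1 places Visit 7 in the long-term follow-up: "subjects will visit the research clinic 6 weeks and 3, 6 and 12 months after treatment (Visit 7 to Visit 10").
- **MAD (Table 8.1-2).** The "Pregnancy test" row is marked at Visit 1 (screening), Visit 2 (Day 1), Visit 12 (Day 21) and Visit 13 (Day 32), and is blank from Visit 14 onwards. Section 8.1.2 puts the last dose on Day 19 and states: "An end-of-treatment phase visit (Visit 13) will take place on Day 32". It also schedules the 6-week visit: "subjects will visit the research clinic 6 weeks and 3, 6 and 12 months after treatment (Visit 14 to Visit 17"). The table header counts the follow-up visits from the end of dosing: "Time points in relation to last dose (Day 19").

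Inclusion criterion 6 in Section 9.4 sets one contraception period for both parts, "until 3 months after the last dose of IMP and until confirmation of negative 6 weeks skin swab and feces analyses".

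**The concern.** The 6-week visit is a checkpoint in both parts, because its swab and feces results form part of the condition for ending contraception. Only the SAD tests for pregnancy there. The difference also runs against exposure: the MAD gives ten doses to four wounds, the SAD one dose to two wounds.

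What is at stake is how soon a pregnancy becomes known. Section 11.7.1.15 requires the outcome of all pregnancies to be followed, which presupposes that the site knows of them. A woman who conceives in the weeks after her last MAD dose would not be found by a scheduled test, whereas a woman at the same point in the SAD could be. Follow-up would be delayed, not prevented.

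**Working it through.** The protocol states no figure for this interval, so there is none to reproduce. The check is a reading of two table rows followed by day arithmetic.

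**Reading the rows.** The SAD pregnancy row has 12 cells under 12 visit columns and the MAD row has 13 under 13. In the MAD table, the adjacent "Urine drug screen" row is marked at every visit from 12 to 21, and the two post-dose pregnancy marks fall under its first two, Visits 12 and 13. The physical examination row, marked from Visit 13 to Visit 21, lines up with the same columns.

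**Inputs from the protocol.** MAD last dose Day 19 ± 1; MAD Visit 13 Day 32 ± 1; SAD Visit 7 and MAD Visit 14 at 6 weeks ± 3 days; MAD Visit 15 at 3 months ± 1 week.

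**Assumptions.** A urine test turns positive 10 to 14 days after conception (not a protocol figure), and 3 months is taken as 91 days.

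**Interval from last dose to last test**

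- MAD: 32 − 19 = 13 days; with windows, 31 − 20 = 11 to 33 − 18 = 15.
- SAD: 6 × 7 = 42 days; with the window, 39 to 45.
- Difference: 42 − 13 = 29 days; with windows, 39 − 15 = 24 to 45 − 11 = 34.

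**Latest conception that the last test can detect, in days after the last dose (interval minus lag, windows included)**

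| Part | Earliest limit | Latest limit | Share of 91 days |
|---|---|---|---|
| MAD | 11 − 14 = −3 | 15 − 10 = +5 | at most 5/91 = 5% |
| SAD | 39 − 14 = 25 | 45 − 10 = 35 | 25/91 = 27% to 35/91 = 38% |

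Conceptions during most of the MAD dosing period are therefore covered by the Day 32 test. Those after it are almost entirely uncovered.

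**Delay if a pregnancy is not reported at MAD Visit 14.** The next visit is Visit 15, 91 − 42 = 49 days later; with windows, 84 − 45 = 39 to 98 − 39 = 59. It has no pregnancy test either.

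**With a test added at MAD Visit 14** (about Day 19 + 42 = Day 61), the limits become 25 to 35 days after the last dose, as in the SAD. The time from the last test to the end of the 91 days falls from 91 − 13 = 78 to 91 − 42 = 49 days.

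**The case against.** The strongest objection is that the mark may simply be in the wrong column. In both tables the first post-dose mark carries the females-only footnote and the second does not. Moving the two MAD marks one column to the right would put them at end of treatment and at 6 weeks, exactly the SAD pattern. The year labels in the header of the MAD table do shift by one column between its repeats in the text as extracted from the PDF. That affects header cells only; the row has the right number of cells and its neighbours align, so the reading stands. If the mark was misplaced in the source, the correction is still a test at Visit 14.

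A second objection is that the harm is thin. In the animal studies no systemic exposure was established and CXCL12 expression was significant for only about an hour. In the MAD the film comes off one hour after each application from Day 3. Subjects use highly effective contraception, and adverse events are asked about at the 6-week and 3-month visits. All of this is true and keeps the absolute risk low. It limits the severity but does not explain why the ten-dose part stops testing sooner.

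Third, the SAD is an imperfect benchmark: on the same assumptions, its last test reaches only 27% to 38% of the contraception period. That also stands. The proposed change makes the two parts consistent; it does not cover the full 3 months.

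Finally, a protocol need not justify every cell of a schedule, and two parts may have different visits. But here the 6-week visit exists in both parts and serves the same contraception condition in both.

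**Conclusion.** The concern holds. The last scheduled pregnancy test comes 13 days (11 to 15) after the last dose in the MAD and 42 days (39 to 45) after it in the SAD, a gap of 29 days (24 to 34), under one contraception rule and without a stated reason. These intervals rest on the protocol alone. The coverage figures (at most 5 days after the last dose in the MAD, 25 to 35 in the SAD) also need the assumed 10 to 14 day detection lag, and the percentages need 3 months taken as 91 days. The point is minor and concerns subject safety in a first-in-human trial of a genetically modified organism. It touches no endpoint, analysis or dose-escalation decision.

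**What to change.** In Table 8.1-2, add a urine pregnancy test (females only) at Visit 14, so that the last test falls 6 weeks after the last dose in both parts. Keep the Day 32 test, which covers most of the dosing period. If the Visit 13 mark was meant for the 6-week visit, the same edit corrects it.

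The cost is one mark in one row and one extra dip test for the women among 24 subjects, on urine already collected at that visit for the drug screen. If the earlier stop was deliberate, Section 11.3.8 should say why, but a stated reason alone would leave the detection gap as it is.
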